## Abstract

**Background:**

The growing number of people with dementia, and the increasing cost of care, provides a major incentive to develop and test methods of supporting them in the community for longer. Most attention has been given to pharmacological interventions, but there is increasing recognition that psychosocial interventions may be equally effective, even preferable where medication has negative side-effects. Reminiscence groups, run by professionals and volunteers, which use photographs, recordings and other objects to trigger personal memories are probably the most popular therapeutic approach to working with people with dementia, but there is little evidence for their effectiveness and cost-effectiveness. The recent inclusion of family carers in groups with people with dementia, notably in our own pilot studies, has generated informal evidence that this joint approach improves relationships between people with dementia and their carers, and benefits both.

**Design and methods:**

This multi-centre, pragmatic randomised controlled trial (RCT) to assess the effectiveness and cost-effectiveness of joint reminiscence groups for people with dementia and their family care-givers has two parallel arms – an intervention group and a control group who receive care as usual. The intervention consists of joint reminiscence groups held weekly for twelve consecutive weeks, followed by monthly maintenance sessions for a further seven months.

The primary outcome measures are the quality of life of people with dementia, as assessed by QoL-AD, and their care-givers' mental health as assessed by the GHQ-28. Secondary outcomes include: the autobiographical memories of people with dementia; the quality of the relationship between them and their care-givers; and the levels of depression and anxiety felt by them and their care-giver. Using a 5% significance level, comparison of 200 pairs attending joint reminiscence groups with 200 pairs receiving usual treatment will yield 80% power to detect a standardised difference of 0.38 in the QoL-AD rated by the person with dementia and 0.28 in the GHQ-28 or carer-rated QoL-AD. The trial will include a cost-effectiveness analysis from a public sector perspective.

**Discussion:**

Our Cochrane review (2005) on reminiscence therapy for people with dementia did not identify any rigorous trials or economic analyses in this field.

**Trial Registration:**

ISRCTN42430123

## Background

The development and evaluation of therapeutic interventions intended to benefit people with dementia and their family carers is the subject of much research interest at present. In view of the large and growing numbers of people with dementia, and the costs associated with meeting needs for care, there are clear advantages for health and social care services in supporting people with dementia in the community for longer but less intensively. However there is consensus that this should not be at the cost of additional burden on family carers [1].

Most attention has been given to pharmacological interventions, but there is increasing recognition that psychosocial interventions may have comparable value [2,3], and may be preferable in some contexts, e.g. where medication may be ineffective or have negative side-effects [3,4]. A number of systematic reviews of psychosocial interventions are now available [e.g. [1,5,6], as well as a number of Cochrane reviews of specific approaches [e.g. [7,8].

In the UK, Reminiscence Therapy appears to be the most well-known therapeutic approach to working with people with dementia. For example, over half of care homes in Wales claim to offer this approach to their residents [9]. Reminiscence work with people with dementia has an extensive history [10,11], engendering enjoyable activities that promote communication and well-being. One factor in its popularity is that it works with early memories, which are often intact for people with dementia, thus drawing on the person's preserved abilities, rather than emphasising the person's impairments. However, its popularity has not led to a corresponding body of evidence on its effects. The existing research literature has been brought together in our revised Cochrane review on reminiscence therapy for people with dementia [12]. Only four randomised controlled trials (RCTs) suitable for analysis were identified. Each examined different types of reminiscence work; all were small or of poor quality. The trials together identified significant improvements in cognition and mood 4–6 weeks after treatment, and stress in care-givers who participated with the person with dementia in a reminiscence group. However, the review concluded that 'in view of the limitations of the studies reviewed, there is an urgent need for more quality research in the field'. This dearth of evidence is reflected in the National Institute for Health and Clinical Excellence and Social Care Institute for Excellence (NICE-SCIE) Guideline on the management and treatment of dementia [3], which found insufficient evidence to recommend that reminiscence should be routinely offered to people with dementia, although its potential impact on mood of the person with dementia was highlighted.

To take research forward, there is a need to specify clearly the exact nature of the reminiscence work to be undertaken and its aims. Typically, a group approach has been implemented, with 'memory triggers' (photographs, recordings, artefacts etc.) used to promote personal and shared memories. A recent development has been to include family carers in reminiscence groups alongside their relatives with dementia. Descriptive evaluations suggest that this joint approach (described as 'Remembering Yesterday Caring Today' – RYCT [13]) may improve the relationship between carer and person with dementia, benefiting both [14]. As it is the breakdown of this care-giving relationship that increases the likelihood of the person with dementia being placed in an alternative care setting, such as a care home, this effect could have far-reaching implications for families, society and public spending. Our group have reported a very small pilot study evaluating this joint reminiscence approach (7 patient-carer pairs in the treatment group; 4 in the waiting-list control group), which showed some trends in improved quality of life for patients and reduced stress for care-givers [15]. In a larger trial platform, funded by the Medical Research Council (MRC), improvements in autobiographical memory and carer depression were associated with reminiscence groups containing 50 patient-carer pairs.

The justification for evaluating the joint reminiscence approach specifically comes from this promising pilot data and the great interest in this approach in the field of reminiscence work [10]. More generally, a recent meta-analysis [1] on interventions with family carers of people with dementia suggested that joint approaches may be more effective in improving carer outcomes than approaches targeted only at the carer. The previous tradition in dementia care of interventions for people with dementia and their carers separate from each other is being questioned. For example, in many areas of the UK, Alzheimer Café sessions have been established, with an agenda including education as well as social contact, attended by both people with dementia and their carers [16]. The emphasis has shifted from 'person-centred care' to 'relationship-centred care', with recognition of the central importance of the relationship between person with dementia and carer to the benefit of both [16]. Although a joint focus on people with dementia and their care-givers is not possible for all people with dementia, only 6% of them have no identifiable care-giver [17], and thus a higher chance of entering care homes.

The objective of this paper is to describe the study protocol of this pragmatic RCT among people with mild to moderate dementia and their family caregivers. The main research questions concern whether reminiscence groups with participants and carers followed by reminiscence-based maintenance are more (cost)-effective in ameliorating the quality of life of people with dementia and the stress on their carers than 'usual treatment'.

## Design and methods

### Design

The design is a pragmatic eight-centre randomised trial (Figure 1). After selection, and baseline assessment, pairs of people with dementia and their family carer are randomised to one of two groups; the intervention group receives usual care plus joint reminiscence groups and reminiscence-based maintenance, the control group receives usual care only. Participants are free to seek additional assistance and support elsewhere at any time after baseline. Participants are allowed to enter the study only after giving signed informed consent in accordance with the provisions of the Mental Capacity Act 2005 [18]. General ethical approval was obtained through the Multi-centre Research Ethics Committee for Wales (ref no. 07/MRE09/58). The study is registered as a clinical trial with ISRCTN 42430123.

**Figure 1 F1:**
[figure not shown]
**Flow diagram for the trial**.

### Participants

Recruitment to this trial is taking place through mental health services for older people in each area (especially Memory Clinics, Community Mental Health Teams for Older People and associated professionals including psychiatrists, occupational therapists and Admiral Nurses), associated day services and through relevant local voluntary sector agencies such as the Alzheimer's Society and Age Concern. Recruitment will be in three waves, giving centres the opportunity to focus on different geographical areas in different waves. The Appendix sets out the inclusion and exclusion criteria for participants in the trial.

### Randomisation

Local researchers, who do not take part in follow-up assessments, contact the remote randomisation service of the North Wales Organisation for Randomised Trials in Health (NWORTH) when they have up to 24 pairs ready for randomisation. NWORTH is accredited as a Clinical Trials Unit by the UK Clinical Research Collaboration (UKCRC) and funded by the Clinical Research Collaboration Cymru, notably for HTA trials. The same researcher arranges for the 12 pairs randomised to the intervention group to attend sessions, and liaises with the group facilitator.

### Blinding

Though participants cannot be blinded to their allocated treatment, all follow-up data are gathered by blinded interviewers. However our experience in the trial platform, shared by similar projects, is that participants may occasionally and inadvertently inform researchers of the treatment they are receiving. We aim to reduce this effect by explicit reminders to participants before the assessment visit and by the use of self-report measures wherever feasible. We also ask all assessors to record their impression of the arm to which each participant belongs, and their confidence in that prediction. This will enable us to test whether inadvertent loss of blinding leads to bias, and to adjust for any bias detected.

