#### Primary outcome measures

a) Quality of life of the person with dementia, using the scale *Quality of Life in Alzheimer's Disease *(QoL-AD) [19], which covers 13 domains of quality of life. This is reliable and valid for people with mild and moderate degrees of dementia when they take part in structured interviews with trained interviewers [20,21].

b) Care-giver's mental health, assessed using the 28-item, self-completed *General Health Questionnaire *GHQ-28 [22] which has been widely used in care-giver research [23,24]; we shall use four-point Likert scales ranging from zero to three. The questionnaire includes indicators of anxiety, depression, insomnia, social dysfunction and somatic symptoms. We chose the GHQ-28 over the Relatives' Stress Scale because it is more general and more widely used.

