### Analysis

#### Statistical Analysis of Effectiveness

We shall analyse by intention to treat and include all available data. However methods of imputing missing data such as last observation carried forward (LOCF) are of limited utility in dementia, where the norm is gradual decline until loss through death and illness. Hence our sample size calculations are based on the numbers we expect to be available at the study end-point, ten months after randomisation. We shall use multi-level modelling to address clustering within randomised groups. We shall use analysis of covariance to adjust for baseline differences in outcome variables. Analyses will treat ten months after randomisation as the primary end-point in evaluating whether the intervention has affected people with dementia or their care-givers. Secondary analyses will focus on effects immediately after the intensive group sessions.

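### The Blinding section commits to adjusting for bias inferred from assessors' guesses of arm, but those guesses can neither show that bias nor validly correct it

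*Protocol article*

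**What the plan says.** The Blinding section states that "all follow-up data are gathered by blinded interviewers", but accepts that "participants may occasionally and inadvertently inform researchers of the treatment they are receiving". Two safeguards are named: reminders to participants before the visit, and self-report measures where feasible. The section continues: "We also ask all assessors to record their impression of the arm to which each participant belongs, and their confidence in that prediction". The purpose follows: "This will enable us to test whether inadvertent loss of blinding leads to bias, and to adjust for any bias detected". No method of testing or adjusting is given, no threshold is set, and nothing calls the exercise exploratory or a sensitivity analysis.

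The section Statistical Analysis of Effectiveness describes intention to treat, multi-level modelling for clustering, and one kind of covariate adjustment: "We shall use analysis of covariance to adjust for baseline differences in outcome variables". It neither includes nor excludes the guess.

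Under Primary outcome measures, the QoL-AD is described as reliable and valid for people with mild and moderate dementia "when they take part in structured interviews with trained interviewers". The other primary outcome is self-completed: "Care-giver's mental health, assessed using the 28-item, self-completed" GHQ-28. Under Secondary outcome measures, the CSDD and RAID are interview-based ratings.

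**The concern.** The sentence sets out a two-step rule: test for bias using the guess, then adjust if bias is found. Both steps have the same weakness.

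An assessor may guess correctly because the participant disclosed the arm. An assessor who has been told nothing has little to go on except how the participant seems to be doing, and that is close to the outcome itself. The guess is then a common effect of allocation and outcome. Guess and outcome will be associated even when every rating is honest, so the association is not evidence of bias. Conditioning on a common effect of arm and outcome also distorts the comparison that randomisation protects. If the treatment helps, part of the benefit is credited to the guess. If it does nothing, the adjusted comparison drifts towards apparent harm.

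At stake is the estimate for the patient-rated QoL-AD, a primary outcome that also feeds the cost-effectiveness analysis, and for the interviewer-rated CSDD and RAID. Because adjustment depends on what is detected, the choice of estimate would also be made after seeing the data.

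**Working it through.** **The plan's own figure.** The Sample size section gives 200 completing pairs per arm, 5% significance (two-sided assumed) and 80% power at 0.28 SD without clustering. Power = Φ(0.28 × √(200/2) − 1.96) = Φ(2.80 − 1.96) = Φ(0.84) = 0.80. This reproduces. With baseline adjustment and an assumed baseline correlation of 0.6, the residual SD is √(1 − 0.36) = 0.8, and power is Φ(2.80/0.8 − 1.96) = Φ(1.54) = 0.94.

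**Set-up.** Outcome y = 0.6x + 0.8e + d·t, where x is baseline, e is noise and t is arm; higher is better; 200 per arm; no assessor bias. Regress y on t and x, with and without the guess. The documents say nothing about how guesses arise, so two models are assumed:
- *Occasional disclosure.* With probability r the guess is the true arm. Otherwise the log-odds of guessing intervention rise by g per SD of outcome.
- *Frequent correct guessing.* logit P(guess = intervention) = L(2t − 1) + g·y, with L = 0.7 or 1.2. This gives about 67% or 77% correct guesses.

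**Results** (3,000 replicates per row; unadjusted estimate 0.28, power about 94%):

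| Guess model | g | Adjusted estimate, d = 0.28 | Power | Adjusted estimate, d = 0 | Type I error |
|---|---|---|---|---|---|
| 5–10% disclosure | 0 | 0.28 | 93–94% | 0.00 | 5% |
| 5% disclosure | 0.5 | 0.26 | 90% | −0.02 | 6% |
| 5% disclosure | 1 | 0.22 | 83% | −0.02 | 6% |
| 10% disclosure | 0.5 | 0.24 | 86% | −0.03 | 7% |
| 10% disclosure | 1 | 0.20 | 74% | −0.05 | 10% |
| about 67% correct | 0.5 | 0.17 | 54% | −0.10 | 22% |
| about 77% correct | 0.5 | 0.11 | 23% | −0.16 | 40% |

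Repeat runs move these slightly; the 10%, g = 1 row comes out at 0.20 or 0.21. With g = 0 and 67–77% correct guesses the estimate also stays at 0.28, and power falls to 91% and 84%.

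**How far the last two rows are from the text.** If undisclosed guesses are at chance, accuracy = r + (1 − r)/2, so r = 2 × accuracy − 1. Accuracy of 67% and 77% then needs r = 0.34 and 0.54, which is far from occasional disclosure.

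**The plan's 0.38.** For the patient-rated QoL-AD the plan uses 0.38 SD. Without a baseline covariate and at 10% disclosure, the adjusted estimate is 0.32 (g = 0.5) or 0.25 (g = 1).

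**Does adjustment repair real assessor bias?** Add 0.4 SD of assessor bias among disclosed participants, with d = 0.28 and no baseline covariate. The value to recover is 0.28.

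| r | Unadjusted | Adjusted, g = 0 | Adjusted, g = 1 |
|---|---|---|---|
| 0.1 | 0.32 | 0.31 | 0.20 |
| 0.3 | 0.40 | 0.37 | 0.15 |
| 0.5 | 0.48 | 0.41 | 0.11 |

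With g = 0, at r = 0.5, the excess falls from 0.48 − 0.28 = 0.20 to 0.41 − 0.28 = 0.13, so most of the bias remains. With g = 1 the estimate overshoots below the truth. Neither case recovers 0.28.

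No simulation includes clustering. The plan's inflation factor of 1.74 would lower the power figures for the patient-rated QoL-AD. Here the simulations serve to show the shift in the estimate.

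**The case against.** The strongest reply is that the protocol does not state the method criticised here. It does not say that the guess becomes a covariate or that the primary model changes, and the analysis section names only baseline adjustment. A statistical analysis plan, not shown, may place any such analysis among the sensitivity analyses. This stands, and it limits the finding. A reader might infer that the primary analysis is already fixed as guess-adjusted and will lose most of its effect and power. The documents do not support that.

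Second, dependence of the guess on outcome is an inference that no section states. Without it, adjustment costs some precision but adds no bias. This stands too, although the inference is reasonable when the interviewer who guesses also gathers the follow-up data.

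Third, the large losses need far more disclosure than the protocol expects. At 5–10% disclosure the harm is modest to moderate. The large figures are an upper scenario and not a forecast.

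Fourth, assessors also record their confidence, which may partly separate near-certain disclosure from a hunch. It may help description. It is an imperfect separator, and the simulations leave it out.

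Fifth, the GHQ-28 is self-completed, so assessor bias is least plausible for one of the two primary outcomes.

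What remains is the sentence itself: an open commitment to adjust for whatever is detected, with no restriction to a secondary role and no acknowledgement that the guess may reflect the outcome.

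**Conclusion.** The point holds in this form: the plan commits to test for and adjust for bias using a post-randomisation guess, without a method and without confining it to a sensitivity analysis. The guess cannot show that bias has occurred, and an estimate adjusted for it is not the intention-to-treat effect that the analysis section promises.

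With a true effect of 0.28 SD and no assessor bias, the adjusted estimate is about 0.20 to 0.26 at 5–10% disclosure with g between 0.5 and 1. It is about 0.11 to 0.17 if 67–77% of guesses are correct with g = 0.5, and unbiased if guesses are unrelated to outcome. Disclosure rate, outcome dependence and baseline correlation are all assumed. The logic of the problem needs only that guesses depend on both arm and outcome. The concern applies mainly to the QoL-AD, CSDD and RAID.

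**What to change.** In the Blinding section, replace the commitment to adjust with a statement that the primary estimate stays as described under Statistical Analysis of Effectiveness and is not adjusted for the assessor's guess. Report guess accuracy and confidence by arm, for example as a blinding index. Label any analysis that uses the guess as an exploratory sensitivity analysis without causal interpretation. Settle this before any unblinded analysis.

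The cost is about one sentence, since guess and confidence are already collected. Recording why the assessor made the guess (disclosure or impression) would help interpretation but is optional, and would be one new form item.

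The downside is that the plan gives up a formal correction for loss of blinding. The guess data cannot validly supply one, so the reminders and self-report measures remain the protection against this bias.

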### Intervention

The practice of using joint reminiscence groups attended by people with dementia and their carers [13] emphasises active, as well as passive, forms of reminiscence by both carers and the people with dementia. Pairs attend 12 two-hour sessions, where possible in a social not clinical setting. Each session focuses on a different theme, including childhood, schooldays, working life, marriage, and holidays and journeys. Couples are encouraged to contribute with materials brought from home. Each session blends work in large and small groups, and a range of activities including art, cooking, physical re-enactment of memories, singing and oral reminiscence. The inclusion of the person with dementia is paramount. In the joint reminiscence groups facilitators and volunteers guide carers to allow the person with dementia to respond and to value their contribution.

There is a limit of 12 pairs for the two trained facilitators in each group, supported by several trained volunteers. Our previous experience suggested that ideally these volunteers should cover a range of ages and come from the voluntary sector (e.g. Alzheimer's Society and Age Concern), health professional trainees and former carers with an understanding of working with older people. The training programme for facilitators and volunteers is set out in the RYCT manual, developed during the MRC trial platform [13]. Training engenders skills in listening, interpreting behaviours group dynamics, and enthusing carers and people with dementia. Two half-day training sessions take place before each group commences. After each session there is time for facilitators and volunteers to prepare session notes, complete attendance forms and collate evaluation forms. These evaluation forms are collected from carers and people with dementia at the end of the first session and at the end of the 12-week programme. The RYCT manual recommends a blend of activities for each session, based on core principles.

The presence of volunteers means that if, for any reason, carers are not able to attend all the group sessions, the person with dementia can still contribute to the group sessions. Subsequent maintenance sessions are held monthly and follow a similar pattern – re-visiting some topics and introducing new topics like a particular decade, for example the 1950s with the aid of relevant music and video clips.

